### Statistical analysis

All data analysis was performed using Stata V16/MP (Stata Corporation, College Station, TX, USA).

To describe the overlap of the three conditions, a Venn diagram will be produced. Due to the lack of independence as the conditions overlap prevalence estimates and the corresponding confidence intervals will be calculated for each segment.

Estimates of prevalence for malnutrition, frailty and sarcopenia will be calculated for the number of older people included at baseline in the study. The number identified with each condition of interest (numerator) will be divided by the total sample (denominator). The resulting proportion will be multiplied by 100,000 to give the number with each condition per 100,000 persons aged over 50 years old in the population. This ‘crude’ estimate is likely to be biased due to differences between the age and gender structure of the Biobank and the UK population. To provide a more representative estimate of prevalence, a direct standardisation approach will be applied. The Biobank sample will be stratified by age groups (e.g., 50–54, 55–59, 60–64, etc.) and gender (male/female), and the prevalence within each group will be estimated. These will then be weighted (using direct standardisation) based on the age and gender population of the UK. This comparison population for the UK will be obtained from the Office of National Statistics for the equivalent time period (2008). If possible, we will repeat the direct standardisation adjustment for ethnicity, socioeconomic status and education level. In each case, 95% confidence intervals will be calculated for the population proportion.

To compare the agreement between the two methods used to measure frailty, we will describe and compare the proportion estimate based on the overlap in 95% confidence intervals and the level of agreement with a Kappa comparison. The Kappa comparison indicates the level of agreement compared to random chance alone. In this comparison, a value of one means a perfect agreement compared to zero, which indicates a level of agreement no better than random chance alone. For intermediate values, Landis and Koch (1977) suggested the following interpretations: below 0.0: poor; 0.00–0.20: slight; 0.21–0.40: fair; 0.41–0.60: moderate; 0.61–0.80: substantial; 0.81–1.00: almost perfect.

From the baseline assessment, details of the participants’ characteristics anthropometric measurements, participants’ medical histories, smoking status, uses of medications, dietary intake records and alcohol intake will be used. This descriptive information will be considered covariates. In this study any missing data present in the key variables related to determining the outcome, i.e., the presence of the condition, as well as the key descriptive covariates, will be described and details will be given on how the variables influence the results.

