### Eligibility and exclusion criteria

The participants included in the study will be both male and female, aged 50 years or older, who completed a touchscreen questionnaire, and physical measurements. Any participant who is under 50 will be excluded.

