### Study sample size

This study will be a subset of the main sample size from the UK Biobank, and it is anticipated 381,000 participants will meet the inclusion criteria (76% of the total sample of participants in the UK Biobank, who met the inclusion criteria age 50 and above) [29].

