#### Mapping frailty to biobank variables

Two models will be used to define frailty and compared. Only one model will be used to consider the overlap with malnutrition and sarcopenia. The 36 deficits model, has been constructed and validated, and applied to large data sets previously [39]. It will be matched to equivalent variables recorded in the UK Biobank. These are listed in S1 Table. The cumulative deficit model calculates the FI by defining the numbers of health deficits present in a person and then dividing by the number of health deficits considered [38, 41]. For instance, a participant with three deficits would have an index score of 3, which out of 36 equals a 0.083 FI. The threshold levels will be: low (robust), where the FI is less than or equal to 0.2; medium (pre-frail), where the FI is more than 0.2 and less than or equal to 0.35; and high (frail), where the FI is more than 0.35. These levels were suggested by Kulminski and colleagues and used in studies that looked at frailty, bone health, and overall mortality [53, 54].

The phenotype model, includes five criteria that will also be mapped with available variables in the UK Biobank. The first four criteria are derived from the self-reported variables entered by participants including: weight loss, exhaustion, slow walking pace and low physical activity. Hand grip strength is a measured variable See Table 2. These criteria were previously used in two studies based on the UK Biobank database [29, 55]. Participants will be classified as robust (met none of the frailty criteria), pre-frail (met one or two of the criteria) or frail (met three or more of the criteria) according to cut-offs described by Fried and colleagues [35]. This is done to ensure consistency with the existing literature, refer to Table 3.

**Table 3 pone.0278371.t003:** Mapping the phenotype model.

Variable	Data Description	Categories Description/Units
weight loss	The information is provided by the participants’ answer to the question ‘compared with one year ago, has your weight changed?’	Response: yes, lost weight = 1, other = 0
exhaustion	Determined by the question ‘over the past two weeks, how often have you felt tired or had little energy?’	Response: more than half the days or nearly every day = 1, other = 0
walking speed	Determined from answers to the question ‘how would you describe your usual walking pace?	(1) slow pace (2) steady/average pace or (3) brisk pace

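### Dividing by the total sample counts participants with missing defining inputs as free of the condition, which biases prevalence down, plausibly most for malnutrition

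*Protocol article*

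**What the plan says.** All references are to the protocol article.

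- **Statistical analysis** sets one rule for all three conditions: "The number identified with each condition of interest (numerator) will be divided by the total sample (denominator"). The result is scaled: "The resulting proportion will be multiplied by 100,000 to give the number with each condition per 100,000 persons aged over 50 years old". It is then standardised directly to the UK age and gender structure. On precision: "In each case, 95% confidence intervals will be calculated for the population proportion".
- **Eligibility and exclusion criteria** admits people aged 50 or older "who completed a touchscreen questionnaire, and physical measurements". CRP and dietary recall are not named.
- **Mapping malnutrition to biobank variables** requires one phenotypic criterion (low BMI, weight loss or low fat-free mass index) plus one aetiological criterion (reduced energy intake or inflammation judged by CRP). Table 2 lists a food frequency questionnaire (FFQ) and a 24-hour recall as the dietary source.
- **Table 3** codes weight loss as "Response: yes, lost weight = 1, other = 0". Exhaustion has the same residual code of 0. The other three phenotype items have no such code.
- **Statistical analysis**, last paragraph, promises that "any missing data present in the key variables related to determining the outcome, i.e., the presence of the condition" will be described, with details on how the variables influence the results. It sets no rule for classification or for the denominator.

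**The concern.** A participant is identified as a case only if enough inputs are recorded to meet the definition. Take someone with low BMI, a normal CRP and no intake value. That person may or may not be malnourished, but the stated rule counts them as not malnourished. The error runs one way: missing inputs can remove cases from the numerator and cannot add any.

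Prevalence and overlap are the study's outputs. A missed malnutrition case moves to the segment with none of the three conditions or, if also frail or sarcopenic, to a segment with less overlap. Frailty and sarcopenia rest mainly on questionnaire items and physical measurements, which eligibility does require. The loss is therefore plausibly largest for malnutrition, and differences between conditions would partly reflect differences in missingness.

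Direct standardisation reweights the strata and does not recover cases missed within a stratum. Study limitations already expects low prevalence because the cohort is healthier than the population. A shortfall from missing inputs has the same sign and could be taken for that effect.

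**Working it through.** **The plan's own figure.** Study sample size states "it is anticipated 381,000 participants will meet the inclusion criteria", given as "76% of the total sample of participants in the UK Biobank". With about 500,000 in the cohort, 0.76 × 500,000 = 380,000, and 381,000 / 500,000 = 76.2%. The figure reproduces, and N = 381,000 is used below.

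**Inputs that the article does not give.** It states no prevalence and no missing-data rate. The following values are assumptions, taken as mutually independent: phenotypic criterion met 10%, raised CRP 20%, low intake 10%. CRP is complete, and the intake value is missing in a share r.

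**True prevalence.** At least one aetiological criterion: 1 − 0.80 × 0.90 = 0.28. Malnutrition: 0.10 × 0.28 = 2.8%.

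**Reported under the plan.** Where intake is missing, only CRP can identify a case, so the aetiological share is (1 − r) × 0.28 + r × 0.20 = 0.28 − 0.08r. Reported prevalence = 0.10 × (0.28 − 0.08r).

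**Status not determinable.** These people are phenotype-positive with normal CRP and no intake value: 0.10 × 0.80 × r = 0.08r.

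| r | Reported, total sample | Not determinable | Reported / (1 − not determinable) | All inputs recorded |
|---|---|---|---|---|
| 10% | 2.72% | 0.8% | 2.74% | 2.8% |
| 25% | 2.60% | 2.0% | 2.65% | 2.8% |
| 50% | 2.40% | 4.0% | 2.50% | 2.8% |
| 75% | 2.20% | 6.0% | 2.34% | 2.8% |

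At r = 50% the shortfall is 0.4 percentage points, or 400 per 100,000. That is 0.4 / 2.8 = 14% of the true value, and 0.004 × 381,000 = 1,524 people.

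**Against the interval.** The 95% half-width is 1.96 × √(0.024 × 0.976 / 381,000) = 0.049 points at 2.4% and 0.052 points at 2.8%. The shortfall at r = 50% is about 0.4 / 0.049 = 8 half-widths. The shortfall is 0.8r points, so it passes 0.052 once r exceeds 0.052 / 0.8 = 6.5%.

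**Why a denominator of determinable status is not enough.** It removes only the phenotype-positive people whose status is unknown. Phenotype-negative people without an intake value are certain non-cases and stay in. In the table it recovers 0.1 of the 0.4 points at r = 50%.

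**Bounds at r = 50%.** If none of the 4.0% are cases, prevalence is 2.4%. If all are, it is 6.4%. The plan's estimate is the lower bound.

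**If CRP is also missing.** With CRP missing in 10% and r = 50%, independently, the reported value is 0.10 × [1 − (1 − 0.18)(1 − 0.05)] = 0.10 × 0.221 = 2.21%.

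**The case against.** The strongest reply has four parts.

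1. **The definitions are either/or or threshold rules.** A person without an intake value can still be identified through CRP. A person with no phenotypic criterion is not malnourished whatever the rest shows. Frailty needs three of five items, so some missing items do not matter. This stands. A reader might infer that prevalence falls in proportion to the share with any missing input, so that recall missing in half the cohort would halve malnutrition. The definitions do not support that: in the example the loss is 14%.

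2. **Table 3 does not code every non-answer as 0.** This also stands. The residual 0 appears for two of five phenotype items, and it may mean only the other valid answers. The options to decline an answer or not know are listed for baseline characteristics in Table 1, not for the condition items. Table 3 adds to the bias only if 'other' includes non-answers.

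3. **Missingness is limited and will be described.** Eligibility does limit it for most frailty and sarcopenia inputs. Table 2 also lists an FFQ beside the recall, and the baseline questionnaires covered diet, so intake may be better recorded than the recall alone. The article does not say which source yields kcal/day. Describing missing data and its influence helps a reader but leaves the headline estimate unchanged.

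4. **An article leaves such detail to the full plan.** That is fair for imputation models and coding. It does not cover a denominator that the article itself fixes.

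**Conclusion.** The point holds in this form: the stated denominator counts participants who lack the necessary inputs as non-cases, so prevalence is biased down wherever defining inputs are missing for people who have the condition. Malnutrition is plausibly the most exposed, because eligibility does not require its aetiological inputs. That ranking is a judgement from the eligibility wording, not a demonstrated fact.

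The size is unknown from the article. The example (2.4% reported against 2.8% true) rests entirely on assumed and independent values. The comparison with the half-width shows that the reported intervals would not convey an error of this kind. It also reflects the very large N, against which even a modest bias looks large.

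**What to change.** - **Denominator.** For each condition, replace the total sample with participants who have all defining inputs recorded, or multiply impute the missing inputs in the full eligible sample. Do not rely on a denominator of determinable status alone.
- **Intake source.** State whether the FFQ or the 24-hour recall supplies the intake value, since this decides who has complete inputs.
- **Coding.** In Table 3, keep missing values and non-answers separate from 'other'.
- **Overlap.** Build the Venn diagram on participants with complete inputs for all three conditions, or on the imputed data.
- **Reporting.** Give the number with complete inputs per condition, and bounds that count the unclassifiable as none and as all cases.

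**Cost.** The change is wording and recoding, plus an imputation model if that route is chosen. Denominators shrink and intervals widen. In the example with half the intake values missing, n = 190,500 and the half-width at 2.8% becomes 1.96 × √(0.028 × 0.972 / 190,500) = 0.074 points, against 0.052 before. Both routes need an assumption about why inputs are missing. Imputation needs missing at random given the variables in the model. The complete-input estimate needs completeness to be unrelated to the condition within the standardisation strata. The bounds show how much rests on this.

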## Methods/design of UK Biobank

This is a cross-sectional study using participants recruited to the UK Biobank. The UK Biobank is a population-based prospective longitudinal cohort with information on approximately 500,000 people. Participants were recruited from the NHS aged between 40–69 years. However, the database included participants aged 37 to 73 for the baseline visit. Data were collected for the initial assessment visit between 2007 and 2010. This was termed the baseline assessment that will be used for this study. An invitation was sent by mail to people who were living within a reasonable travelling distance from the assessment centres used for data collection. People were recruited from England, Scotland and Wales.

At the baseline assessment visit, all participants had to be able to give consent before starting the assessment. Then a series of assessment stations where undertaken that included a touchscreen questionnaire and an interview questionnaire about diet, cognitive function, work history and digestive health [49]. In addition to demographic data, the participants were given cognitive function tests, their height, hip and waist measurements were recorded, as well as their bioelectrical impedance measurements and hand-grip strength. The UK Biobank database aims to improve prevention, diagnosis and treatment of a broad number of diseases. This detailed information on participants provides a resource for investigators to conduct research relating to particular diseases [49].

The UK Biobank Ethics and Governance Council (EGC) was founded by the Medical Research Council and Wellcome Trust, allowing them to act independently [50]. The UK Biobank controls all access to and use of the data [50]. However, UK Biobank evaluates all proposals to verify that they would be compliant with the participants’ consent and the Biobank’s Governance Framework and have received the required ethics approval [50]. The researcher and collaborators signed a Material Transfer Agreement (MTA) with the UK Biobank. The MTA was submitted and the payment process completed for the approved application, allowing the data to be released to the approved researcher.

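### Prevalence is labelled for persons over 50 with no upper age, but nobody in the sample is older than 73, so the crude and standardised figures can describe only ages 50–73

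*Protocol article*

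**What the plan says.** Four statements in the protocol article bear on the population to which the results apply.

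- **Label (Statistical analysis).** The crude proportion is multiplied up to "give the number with each condition per 100,000 persons aged over 50 years old in the population".
- **Standardisation (Statistical analysis).** Because the crude figure is expected to be biased by the age and gender structure of the Biobank, prevalence is estimated within age and gender strata. The age groups are five-year bands, given as examples from 50–54 upwards, and the last band is not named. Then: "These will then be weighted (using direct standardisation) based on the age and gender population of the UK". The reference population is that of 2008; no upper age is stated for it.
- **Eligibility (Eligibility and exclusion criteria).** There is a floor and no ceiling: "Any participant who is under 50 will be excluded".
- **Ages observed (Methods/design of UK Biobank).** "Participants were recruited from the NHS aged between 40–69 years", and "the database included participants aged 37 to 73 for the baseline visit".

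The Discussion adds that standardisation to a second source will make the findings more generalisable. The Discussion and Study limitations acknowledge that the Biobank is healthier than, and not representative of, the UK population. Neither mentions that the sample has an age ceiling.

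**The concern.** The named population is open at the top, while the data stop at 73. Direct standardisation corrects for a different mix of ages among those who were sampled. It cannot supply a prevalence for ages at which nobody was sampled.

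Prevalence is the means by which the article pursues its aim of describing overlap, so this concerns the main quantity reported. The Abstract calls the three conditions age related, and the Background says that malnutrition generally increases with age and that frailty is associated with ageing. The ages left out are therefore those in which the article itself leads one to expect the highest prevalence. A user who applied a rate labelled as over 50 to a population count of everyone over 50 would understate the number affected. The confidence interval would give no warning, because with so large a sample it is very narrow. The claim of better generalisability would also suggest that the age-structure problem had been dealt with.

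**Working it through.** **1. The plan's own figure.** Study sample size anticipates 381,000 participants, 76% of the cohort; Methods/design of UK Biobank gives about 500,000 in total. 381,000 / 500,000 = 76.2%, and 0.76 × 500,000 = 380,000. The figure reproduces. The problem is one of scope, not of arithmetic.

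**2. Ages supported by the data.** Observed range 37–73, floor 50: the analysis sample covers 50–73. Ages 70–73 lie outside the recruitment range of 40–69 and may be thinly represented.

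**3. What standardisation needs.** The estimator is P = Σ w_k p_k over strata k, with w_k the population share and p_k the sample prevalence. For any stratum made up of ages 74 and over, p_k does not exist. The analyst can

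- limit the weights to observed strata, which gives a valid estimate for 50–73 but leaves the over-50 label wrong; or
- carry the prevalence of the oldest observed band up to all older ages, which is extrapolation.

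The article does not say which. A full 70–74 band would also need care, since its weight includes persons aged 74 whom the sample does not contain.

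**4. Size of the gap if the result is read as over 50.** Let w be the share of persons over 50 who are aged 74 or more, and r the ratio of prevalence at 74+ to the standardised prevalence at 50–73. Then

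P(50+) / P(50–73) = (1 − w) + w·r = 1 + w(r − 1).

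Neither w nor r is in the document. Both are assumed here, over a range:

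| w | r = 1 | r = 1.5 | r = 2 | r = 3 | r = 4 |
|---|---|---|---|---|---|
| 0.15 | 1.000 | 1.075 | 1.150 | 1.300 | 1.450 |
| 0.20 | 1.000 | 1.100 | 1.200 | 1.400 | 1.600 |
| 0.25 | 1.000 | 1.125 | 1.250 | 1.500 | 1.750 |
| 0.30 | 1.000 | 1.150 | 1.300 | 1.600 | 1.900 |

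For r from 1.5 to 4 the ratio runs from 1.075 to 1.90. The reported figure would be too low by 1 − 1/1.075 = 7% up to 1 − 1/1.90 = 47%. At w = 0.25 and r = 2 it would be 1 − 1/1.25 = 20% too low. At r = 1 there is no error.

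**5. Comparison with the sampling interval.** Assume 5% prevalence at 50–73 and n = 381,000. The simple binomial 95% half-width is 1.96 × √(0.05 × 0.95 / 381,000) = 0.00069, or about 69 per 100,000. With w = 0.25 and r = 2 the gap is 5,000 × 0.25 × (2 − 1) = 1,250 per 100,000. At the smallest assumed combination (w = 0.15, r = 1.5) it is 5,000 × 0.075 = 375 per 100,000, still more than five half-widths (375 / 69 = 5.4). A standardised estimate would have a different half-width, but its interval likewise reflects sampling error only.

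**The case against.** The strongest reply is that the section, read naturally, already does the right thing. It stratifies the sample, estimates prevalence in the strata that exist, and weights those. Five-year bands offered as examples are closed bands. Weighting only observed strata is ordinary direct standardisation, and the last band and exact population extract are details that an article may leave to a fuller document.

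Much of this stands. A reader might infer that the plan standardises to all UK persons over 50, or that it will assign the prevalence of the oldest participants to those aged 75 and over. The text says neither. A reader might also infer that the results describe a population that was not observed. That goes too far: ages 50–73 were observed, the range is disclosed, and only ages 74 and over are missing. The sentence carrying the over-50 label describes the crude figure. The standardised figure is offered as its more representative counterpart, and no other target is named for it. The energy-requirement bands in Mapping malnutrition to biobank variables, which end at 74, are consistent with a sample ending at 73 and are no further defect.

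The size also rests wholly on assumed values, and it matters only if the result is read as covering older ages.

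What does not stand is that this removes the point. Even with the weights confined to observed strata, the label names a population wider than the data. A separate analysis plan that capped the age would still conflict with the published label, and the limitations are silent on the ceiling.

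One further mismatch is minor: "People were recruited from England, Scotland and Wales", whereas the standard is the UK. The document gives no basis for expecting an important effect on age and gender weights.

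**Conclusion.** The point holds as a mismatch between the stated target and the ages observed. The crude and standardised prevalences can describe persons aged 50–73 only. If they are labelled and weighted that way, this point requires no further correction to the estimates.

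If they are read as over 50, they are too low to the extent that prevalence is higher at 74 and above, the direction the Abstract and Background lead one to expect. A ratio of roughly 1.1 to 1.9 follows from the assumed share of 15–30% and prevalence ratio of 1.5–4. It illustrates the possible error and is not an estimate of it. One ratio need not suit all three conditions, and the document allows no narrower range.

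The conclusion does not depend on those assumptions, because the label exceeds the data whatever the ratio. It should be corrected before results are reported.

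**What to change.** - Define the target population as persons aged 50–73 in the Statistical analysis section, and state the upper age alongside the eligibility floor.
- Restrict the 2008 population weights to ages 50–73. Name the last band and cut it at 73 (70–73, not 70–74), so that the weights match the ages observed.
- Label every crude and standardised result as per 100,000 aged 50–73.
- Add the age ceiling to Study limitations, and mention it beside the statement in the Discussion that standardisation makes the results more generalisable.
- If the 70–73 group proves sparse, add a sensitivity analysis restricted to 50–69. Making 50–69 the primary range would be a trade-off: it would discard observed participants aged 70–73, for whom the malnutrition mapping sets a separate BMI threshold.

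The cost is wording and a population extract that can be cut at age 73; no new participant data are needed. The downside is a narrower stated target, with no claim about ages 74 and over.
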